## Introduction

1

Perioperative anxiety is a prevalent psychological issue among surgical patients, characterized by a diffuse sense of tension and unease stemming from factors such as the underlying disease, hospitalization, anesthesia, and uncertainty about the surgical procedure (1). It encompasses both preoperative and postoperative anxiety (2). The incidence of perioperative anxiety varies across different disease populations, ranging from 11 to 80% (3). Data from the National Institute of Mental Health indicate that females are more susceptible to various anxiety symptoms than males. Further research reveals that the occurrence of anxiety disorders in females is 1.3 to 2.4 times higher than in males, with this disparity being particularly pronounced during the perioperative period, where the incidence significantly exceeds that in males (4, 5). This gender difference involves both biological factors, such as hormonal influences, as well as psychological and sociocultural factors, including gender role expectations and stress coping strategies (6–8). In the surgical setting and under stressful conditions, the occurrence of perioperative anxiety is significantly increased in female patients, with anxiety levels often peaking on the night before or the morning of operation (5, 9). Preoperative anxiety increases both physiological and psychological burden, adversely affecting short- and long-term recovery outcomes. These include heightened postoperative pain, extended hospital stays, and delayed convalescence (10, 11). Moreover, anxiety is closely associated with other psychiatric conditions such as depression, cognitive decline, and sleep disturbances (12, 13). Thus, early intervention for pre-operative anxiety is important.

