## Randomization and blinding

2.3

This study utilizes a block randomization method. A computer-generated random block sequence of 4 or 6 will be used to centrally randomize participants into either the active rTMS group or the sham rTMS group at a 1:1 ratio. The randomization sequence was generated by an independent researcher from the study team using a computer-based program. This researcher had no involvement in participant recruitment, intervention delivery, outcome assessment, or data analysis. Sequentially numbered, opaque, sealed envelopes were used to ensure allocation concealment. After enrollment and baseline assessment, the envelope was opened by the operator responsible for administering the rTMS at the time of the first rTMS session to determine group assignment. To ensure effective blinding, both groups will use identical stimulation equipment and follow the same operating procedures. However, the device used in the sham rTMS group will not deliver pulsed magnetic fields to the brain; it will only produce sounds and vibrations similar to those generated during actual pulse stimulation. Throughout the study, all other parties, including the participants, outcome assessors, and data analysts, will remain blinded to group assignment.

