## Study interventions

2.5

All rTMS procedures were performed by professionally trained and experienced operators who had undergone standardized training prior to study initiation. The rTMS intervention is administered on the day before surgery and the day of surgery, resulting in two sessions per participant. This protocol is designed to accommodate the limited perioperative time window while providing a rapid, clinically feasible intervention.

Stimulation parameters are based on established neurophysiological principles. The right dorsolateral prefrontal cortex (DLPFC) is selected as the target region due to its role in negative emotional processing and its involvement in anxiety-related neural circuits. Low-frequency (1 Hz) stimulation is applied to reduce cortical excitability and modulate prefrontal–limbic pathways. The entire procedure strictly followed a unified protocol to ensure consistency in coil positioning, stimulation parameters, and patient interaction.

First, a circular coil was used to locate the stimulation target. The primary motor cortex (M1) was clinically identified as the area 2 cm anterior and 1–1.5 cm lateral to the intersection of the naso-occipital line and the temporoparietal line on the patient’s scalp (i.e., the Cz point). The resting motor threshold (RMT) for each patient was then determined as a reference for setting the stimulation intensity, expressed as a percentage of the rTMS device’s maximum output (24). The RMT was defined, using the visual observation technique, as the lowest stimulation intensity capable of eliciting a visible contraction in the target muscle in 5 out of 10 trials while the muscle was completely relaxed (24). Subsequently, a figure-8 coil was used to target the right DLPFC. The center of the coil was positioned parallel to the patient’s scalp, with its midpoint aligned directly over the stimulation site. The rTMS treatment was then delivered at an intensity of 80–120% of the RMT using a low frequency of 1 Hz (21). Both groups will undergo the intervention using identical devices and operational procedures. However, in the sham rTMS group, the device will not deliver pulsed magnetic fields to the brain but will only produce similar audible clicking sounds and scalp sensations/vibrations mimicking those emitted during active stimulation.

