## Anesthesia

2.6

Standard intraoperative monitoring is initiated upon patient arrival in the operating room [e.g., pulse oximetry, electrocardiogram (ECG), non-invasive blood pressure (NIBP), and bispectral index (BIS)].

General anesthesia is induced with 2.0–2.5 mg·kg^−1^ propofol, 0.3–0.5 μg·kg^−1^ sufentanil, and 0.6–1 mg·kg^−1^ rocuronium. Tracheal intubation is performed once BIS falls below 60, and mechanical ventilation is utilized to keep end-expiratory CO₂ between 35 and 45 mmHg. Anesthesia is continued with intravenous propofol (4–6 mg·kg^−1^·h^−1^), remifentanil (0.1–0.3 μg·kg^−1^·min^−1^), and 1% sevoflurane inhalation to keep BIS between 40 and 60. Vasoactive agents are administered as required to keep hemodynamic stability.

Postoperatively, patients are transferred to the post-anesthesia (PACU) or surgical intensive (SICU) care units, and extubation occurs upon recovery of consciousness. Analgesia is provided via patient-controlled intravenous analgesia (PCIA) using 100 μg sufentanil and 8 mg ondansetron diluted to 100 mL with normal saline, with a background infusion of 1.5–2.0 mL·h^−1^ and patient-controlled bolus doses of 1.0–2.0 mL.

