### Primary outcome

2.7.1

The primary outcome is the change in anxiety score from baseline to 3 days post-operation, measured using the HADS-A (25), with a score of ≥8 indicating clinically significant anxiety (26). The minimal clinically important difference (MCID) for the Hospital Anxiety and Depression Scale (HADS) is not fixed and varies across clinical contexts and analytical methods. Evidence from anchor-based studies and systematic reviews suggests that a change of approximately 1.5–2.0 points in the HADS total or subscale scores is generally considered clinically meaningful (27–29). Anxiety was assessed preoperatively in the ward on the day pre-operation (T0) prior to the first rTMS intervention, and the second intervention was administered in the pre-operative holding area on the day of operation. Postoperative anxiety scores were measured on days 1 (T1), 2 (T2), 3 (T3), and the 3rd month post-operation (T4).

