## Statistical analysis

2.11

All analyses will be conducted according to the intention-to-treat (ITT) principle, with participants assessed in their originally assigned groups regardless of protocol adherence or treatment received. Baseline demographic and clinical characteristics will be summarized to evaluate balance between the groups. Continuous variables will be assessed for normality using the Shapiro–Wilk test. Normally distributed variables will be presented as mean ± standard deviation (SD) and compared using independent t-tests, while non-normally distributed variables will be expressed as median (interquartile range, IQR) and analyzed using the Mann–Whitney U test. Categorical variables will be expressed as counts and percentages and compared using the chi-square test or Fisher’s exact test.

The primary outcome will be analyzed using a linear mixed-effects model, including treatment group, time, and treatment-by-time interaction as fixed effects, and a random intercept for each subject to account for within-subject correlations. Baseline HADS-A score, age, type of surgery, and relevant perioperative variables (e.g., anesthesia duration) will be included as covariates to control for potential confounding.

Secondary outcomes will be assessed via a linear mixed-effects model, comprising baseline values as covariates. Fixed effects will involve treatment, time, and the treatment-by-time interaction, with a random intercept for subjects accounting for within-subject variability. The treatment-by-time interaction will be initially examined. If significant, group differences and within-group changes at each time point will be assessed, with Bonferroni correction applied for multiple comparisons of baseline changes in anxiety scores. If not significant, only the major effect of treatment will be evaluated, and no Bonferroni correction will be utilized for time-specific treatment effects. Binary outcomes will be compared via the *χ*^2^ test or Fisher’s exact test, with relative risk (RR) and 95% confidence intervals (CI) reported.

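### The primary model adjusts for anesthesia duration, which is known only after randomization and both rTMS sessions, so the treatment coefficient is not guaranteed to equal the total effect of assignment

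*Protocol article*

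**What the plan says.** Section 2.11 of the protocol article specifies a linear mixed-effects model for the primary outcome, with group, time and their interaction, a random intercept, and these covariates: baseline HADS-A, age, type of surgery, and a last item described as "relevant perioperative variables (e.g., anesthesia duration) will be included as covariates to control for potential confounding". The same section opens with "All analyses will be conducted according to the intention-to-treat (ITT) principle".

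Three other places fix the order of events:

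- 2.3 Randomization and blinding: "the envelope was opened by the operator responsible for administering the rTMS at the time of the first rTMS session".
- 2.5 Study interventions: "The rTMS intervention is administered on the day before surgery and the day of surgery, resulting in two sessions per participant".
- 2.7.1 Primary outcome: "the second intervention was administered in the pre-operative holding area on the day of operation".

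The article names no unadjusted or baseline-only primary analysis, and it does not confine the perioperative variables to those known before randomization.

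**The concern.** Baseline covariates in a randomized trial serve precision and deal with chance imbalance. A variable that arises after treatment does neither job cleanly. Confounding of assignment is already excluded by design, so the reason given for including anesthesia duration does not hold.

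Two mechanisms could then pull the treatment coefficient away from the effect of being assigned to rTMS:

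- **Blocked mediation.** If rTMS alters duration and duration alters postoperative anxiety, holding duration constant removes that part of the effect.
- **Collider bias.** If rTMS alters duration and an unmeasured cause drives both duration and anxiety, conditioning on duration links assignment to that cause.

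The primary estimate is what is at stake. The wording also lets in further intraoperative or postoperative variables, to which the same argument would apply.

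**Working it through.** **1. Order of events (from 2.3, 2.5, 2.6 and 2.7.1).** Baseline HADS-A is taken before the first session. The envelope is opened at the first session, on the day before surgery. The second session is given in the holding area on the day of surgery. Anesthesia follows. Duration is thus known only after allocation and after the whole intervention. Baseline HADS-A, age and planned type of surgery are known before it.

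**2. The plan's own figure (2.10 Sample size).** Inputs: difference 1.3, SD 2.9, alpha 0.05 (two-sided assumed), power 0.80.

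n per group = 2 × (1.960 + 0.842)² × 2.9² / 1.3² ≈ 78.1, so 79 when rounded up. The t-test version gives 79.1, so 80. The stated 78 is reproduced to within two patients. (One-sided testing would give 62, which does not match.) The point below does not depend on this figure; it supplies only the 1.3 and the 2.9.

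**3. What adjustment does.** This is a simplified linear model for one time point. Let Z be assignment, M duration in SD units (within-arm variance 1), and U an unmeasured cause with variance 1:

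- M = aZ + cU + error
- Y = dZ + bM + gU + error
- total effect of assignment = d + ab
- coefficient of Z adjusted for M = total − a(b + gc)

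The term b + gc is the within-arm slope of HADS-A on duration. The estimate therefore moves by (shift in duration) × (within-arm slope), and by nothing if either is zero.

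**4. Numbers.** The protocol gives neither a nor the slope, so both are assumptions. Take a total effect of −1.3 and a slope of 0.5 points per SD. That slope can arise from mediation alone (b = 0.5, g = 0) or from a shared cause alone (b = 0, g = 1.0, c = 0.5); the result is the same.

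| Shift a (SD) | Adjusted coefficient | Movement | Share of 1.3 |
|---|---|---|---|
| 0 | −1.30 | 0 | 0% |
| −0.1 | −1.25 | 0.05 | 4% |
| −0.2 | −1.20 | 0.10 | 8% |
| −0.3 | −1.15 | 0.15 | 12% |

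Simulation with 2,000,000 patients per scenario agreed with the formula to within about 0.006 points. The table shows attenuation because a shorter duration is paired with a positive slope. If a and the slope had the same sign, the estimate would move away from zero. The documents do not settle the direction.

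**5. Is the covariate needed for precision?** With 126 per group less 10% dropout (126 × 0.9 = 113.4, so 113), power for 1.3 points at SD 2.9 is about 92%. With all 126 it is about 94%. Neither figure relies on covariate adjustment.

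**The case against.** The strongest reply is that no mechanism is documented for this particular covariate. The Introduction lists harms of preoperative anxiety ("These include heightened postoperative pain, extended hospital stays, and delayed convalescence"), but anesthesia duration is not among them. Section 2.6 Anesthesia ties drug delivery to patient response ("1% sevoflurane inhalation to keep BIS between 40 and 60") and says that "extubation occurs upon recovery of consciousness". Titration governs how much drug is given, not how long the operation lasts. Extubation is described after transfer out of the operating room, and the article does not say whether that time counts as anesthesia duration. If duration is set by the operation, rTMS does not move it and there is no bias. In particular, if rTMS does nothing at all, this adjustment creates no spurious effect. All of that stands, and it is why the conclusion is conditional.

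A reader might infer three stronger things that the documents do not support:

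- **That the plan contradicts its intention-to-treat principle.** Section 2.11 explains that principle as analysis by assigned group whatever the adherence or treatment received. A covariate neither reassigns nor excludes anyone. The issue is which effect the coefficient estimates.
- **That the bias could reach about a third of the planned effect.** This needs a slope of about 1.5 points per SD (0.3 × 1.5 = 0.45; 0.45 / 1.3 = 35%). Against an SD of 2.9, that slope means duration explains (1.5 / 2.9)² ≈ 27% of outcome variance, which is hard to reconcile with a covariate expected to add little once type of surgery is in the model. A slope of 0.5 corresponds to (0.5 / 2.9)² ≈ 3%.
- **That covariates will be picked after seeing the data.** Nothing says so. The full list may be closed in an analysis plan that is not shown, and some of the unnamed variables may be preoperative. Only anesthesia duration is shown to be post-randomization.

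What the reply does not rescue is the stated choice itself. Duration is named for the primary model, the reason given is mistaken, and the article does not argue that rTMS leaves duration unaffected.

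**Conclusion.** The point holds in conditional form. Adjusting the primary model for anesthesia duration has no role in controlling confounding of a randomized assignment, and it means the treatment coefficient is no longer guaranteed to equal the total effect of assignment. It would be wrong to say that the coefficient definitely is not that effect, because the two coincide if rTMS does not shift duration or if duration is unrelated to HADS-A within arm.

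Under an assumed shift of 0 to 0.3 SD and a slope of 0.5 points per SD, the movement is 0 to 0.15 points, or 0 to 12% of 1.3. Both inputs are assumptions, and the direction is unknown. The change should be made because it protects the primary estimate at almost no cost; the likely size does not make it critical.

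**What to change.** In 2.11, drop the perioperative-variables item, including anesthesia duration, and the confounding rationale from the primary model. Suggested text:

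> *The primary model adjusts only for covariates fixed before randomization: baseline HADS-A, age and planned type of surgery. Any model that also includes anesthesia duration or another variable arising after randomization is a sensitivity or exploratory analysis and is labelled as such.*

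Planned, rather than performed, type of surgery keeps that covariate free of intraoperative changes. Anesthesia duration can also be summarized by arm.

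The cost is one sentence in the protocol or analysis plan, ideally before unblinding. It needs no extra patients or data and leaves the target of 126 per group unchanged.

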### Secondary outcomes

2.7.2

Secondary outcomes comprise: anxiety scores (T1–T4); occurrence of post-operative delirium [evaluated via the Confusion Assessment Technique for the ICU (30) during T1–T3]; pain scores [10-point Numeric Rating Scale (NRS) (31) during T1–T3, 0 = no pain, 10 = worst imaginable pain]; frailty scores [FRAIL Index (32) during T1–T4, 0 = most robust, 5 = most frail]; and sleep quality [Pittsburgh Sleep Quality Index (PSQI) (33) during T1–T4, 0–21, higher scores denote poorer sleep].

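### The secondary mixed models adjust only for baseline values that pain, frailty and sleep are not scheduled to have, and leave out prognostic covariates already recorded for the primary model

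*Protocol article*

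**What the plan says.** Section 2.11 describes two linear mixed models in consecutive paragraphs. For the primary outcome: "Baseline HADS-A score, age, type of surgery, and relevant perioperative variables (e.g., anesthesia duration) will be included as covariates to control for potential confounding". For the secondary outcomes: "Secondary outcomes will be assessed via a linear mixed-effects model, comprising baseline values as covariates". The remaining structure is the same in both. For the secondary models it reads: "Fixed effects will involve treatment, time, and the treatment-by-time interaction, with a random intercept for subjects accounting for within-subject variability".

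Section 2.7.2 gives the measurement times. Pain is listed as "pain scores [10-point Numeric Rating Scale (NRS) (31) during T1–T3", and frailty and sleep as T1 to T4. Table 1 agrees: its column for the day before the operation is marked for HADS-A and is blank for NRS, FRAIL and PSQI.

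HADS-A at day 3 (T3) appears twice. Section 2.7.1 says "The primary outcome is the change in anxiety score from baseline to 3 days post-operation, measured using the HADS-A", and section 2.7.2 begins "Secondary outcomes comprise: anxiety scores (T1–T4", a range that includes T3.

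**The concern.** The only covariate named for the secondary models is a baseline value, and three of the four secondary scales have no scheduled baseline. Those three would be compared with no adjustment, although age, type of surgery and baseline HADS-A are in hand before treatment starts.

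The protocol gives grounds for expecting these variables to be prognostic. Its Introduction says "Preoperative anxiety increases both physiological and psychological burden, adversely affecting short- and long-term recovery outcomes", names greater postoperative pain among the consequences, and links anxiety to sleep disturbance. Section 2.2.1 admits women of any age from 18 having any operation under general anesthesia, so age and procedure will vary widely. Section 2.3 describes block randomization and mentions no stratification, so chance imbalance in surgery type would be handled only through the model.

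A smaller matter is that day-3 HADS-A is covered by both models, which differ in their covariates. Two slightly different estimates of the same contrast could be reported.

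**Working it through.** **The plan's own figure.** Section 2.10 gives a difference of 1.3, SD 2.9, alpha 0.05, power 0.80 and 78 per group. Two-sided normal approximation: 2 × (2.9 × (1.960 + 0.842) / 1.3)² = 78.1. This reproduces the stated figure up to rounding (79 if rounded up). After 10% dropout, 126 × 0.9 = 113.4, so about 113 per group remain.

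**Covariates available to each model, as written.**

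| Outcome | Own baseline scheduled? | Recorded covariates left out |
|---|---|---|
| NRS pain | No | Baseline HADS-A, age, type of surgery |
| FRAIL | No | Baseline HADS-A, age, type of surgery |
| PSQI | No | Baseline HADS-A, age, type of surgery |
| HADS-A, T1–T4 | Yes (T0) | Age, type of surgery (and perioperative variables) |

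Delirium is binary, is compared by chi-square or Fisher's exact test, and lies outside this point.

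**Precision.** Let R² be the share of outcome variance explained by the omitted covariates. The documents give no value, so a range is assumed. Adjustment multiplies the standard error of a group difference by √(1 − R²). Intervals are then narrower by 1 − √(1 − R²), and the equivalent number of extra patients is 252/(1 − R²) − 252.

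| Assumed R² | Interval narrower by | Equivalent extra patients |
|---|---|---|
| 0.02 | 1.0% | 5 |
| 0.05 | 2.5% | 13 |
| 0.10 | 5.1% | 28 |
| 0.20 | 10.6% | 63 |
| 0.30 | 16.3% | 108 |

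This applies to group differences at a time point. In complete, balanced data, covariates that are constant over time leave the treatment-by-time test essentially unchanged.

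**Bias.** In 3,000 simulated trials (113 per arm, SD 2.9, true difference −1.3, R² = 0.10, regression at one time point), the mean estimate was −1.30 both with and without the covariate. Its SD was 0.368 with and 0.388 without. Only precision is affected.

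**Day-3 HADS-A under two models.** With baseline as a covariate, change and raw score give the same treatment effect, so both models estimate one quantity. The less-adjusted standard error is 2.9 × √(2/113) = 0.386. At R² = 0.10 the adjusted one is 0.386 × √0.9 = 0.366. The two estimates differ by chance with SD about 0.386 × √0.10 = 0.12 points (0.125 in the simulation). Over R² from 0.02 to 0.30 this SD runs from 0.06 to 0.21 points.

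**The case against.** The strongest reply is that an article condenses the plan, and a full covariate list per secondary outcome is normally left to the analysis plan. The wording is also open: it does not say that baseline values means the outcome's own baseline, and it does not expressly exclude age or surgery type. This has some force. Section 2.11 also uses PSQI and FRAIL to define subgroups, which might suggest preoperative scores are taken, but no stated schedule shows them. Still, the article does name covariates for both sets of models, and names different ones. The covariate it names for the secondary models does not match its own schedule for three scales. That is a mismatch in what is stated, not missing detail.

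It is also fair that the gain may be small. No R² is given, the Introduction reports associations rather than shares of variance, and entry at HADS-A of 8 or more restricts the range of baseline HADS-A and so weakens it as a predictor. All of this stands.

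Three stronger readings are tempting and are not supported:

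- **Baseline HADS-A is missing from every secondary model.** It is not. In the secondary anxiety model it is the baseline value.
- **The secondary comparisons are invalid.** They are not. A less-adjusted comparison in a randomized trial is unbiased.
- **Testing day-3 HADS-A twice raises the false-positive rate to 6–7%.** That figure belongs to two ungated tests, each at 0.05, with R² of 10–20%. Section 2.11 examines the interaction first and applies Bonferroni to the anxiety changes if it is significant; otherwise only the main treatment effect is evaluated. Under that rule the chance that either day-3 test is positive was 4.8–5.3%, at most 0.02 percentage points above the primary test alone. This comes from 20,000 simulated null trials per setting, with 113 per arm, four time points, Bonferroni by four, within-subject correlation 0.5 or 0.7, R² 0.1 or 0.2, and a balanced approximation to the mixed model.

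**Conclusion.** The point holds as one of efficiency and consistency. As written, the pain, frailty and sleep models have no usable baseline covariate and omit three recorded prognostic candidates; the secondary HADS-A model omits only age and type of surgery (and the perioperative variables). The loss ranges from negligible (intervals about 1% narrower with adjustment at R² = 0.02) to worthwhile (about 16% at R² = 0.30). Which applies cannot be told from the documents. The conclusion rests on reading baseline values as the outcome's own baseline, and on Table 1 and section 2.7.2 being complete.

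The day-3 overlap is real but minor. The primary outcome has its own assigned model, and nothing in the text lets the secondary model replace it.

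**What to change.** In section 2.11, state that the pain, frailty and sleep mixed models include baseline HADS-A, age and type of surgery, plus the scale's own baseline where it is measured. Restrict these additions to variables fixed before randomization. Anesthesia duration arises afterwards and should not be carried over.

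For HADS-A, adjust the secondary analysis for age and type of surgery as well. The simplest way is to report the T3 contrast once, from the primary model, and to take the T1, T2 and T4 contrasts from that same model. Section 2.7.2 would then list only T1, T2 and T4 for anxiety. Whether the primary model should keep its perioperative variables is a separate question that this change does not settle.

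The cost is a sentence or two in section 2.11 and a small edit in section 2.7.2. No new data or patients are needed. The models lose a few degrees of freedom, depending on how many surgery categories are used, a number the article does not give.

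### Gated within-arm tests of HADS-A change can show a significant fall without any rTMS effect, because patients are selected on a high baseline score

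*Protocol article*

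**What the plan says.** Protocol section 2.2.1 admits only patients with HADS-A of at least 8. Section 2.7.1 fixes the baseline: "Anxiety was assessed preoperatively in the ward on the day pre-operation (T0) prior to the first rTMS intervention". Table 1 shows a single pre-operative HADS-A, so the score that selects the patient is apparently also the baseline. The Introduction states that anxiety often peaks the night before or the morning of surgery, which places T0 close to that peak.

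The paragraph on secondary outcomes in section 2.11, which covers anxiety at T1–T4, sets up a two-step procedure. First, "The treatment-by-time interaction will be initially examined". A positive result there leads to the second step, in which "group differences and within-group changes at each time point will be assessed". The same sentence adds a multiplicity rule for this step, namely "with Bonferroni correction applied for multiple comparisons of baseline changes in anxiety scores". Otherwise, "If not significant, only the major effect of treatment will be evaluated". The number of comparisons in the Bonferroni family is not given.

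The primary analysis is separate and compares the arms: "The primary outcome will be analyzed using a linear mixed-effects model, including treatment group, time, and treatment-by-time interaction as fixed effects". Its covariates begin with "Baseline HADS-A score, age, type of surgery, and relevant perioperative variables".

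**The concern.** When patients are selected because a score is high, and that score is also the baseline, the next measurement tends to be lower even if nothing has been done. A baseline taken near a natural peak pushes the same way, for a different reason. Both effects are equal in expectation in the two randomised arms, so the sham contrast removes them. A test of change within one arm does not use that contrast, so it cannot separate rTMS from selection and time.

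The risk is a secondary result that looks confirmatory: a corrected, significant fall from baseline in the rTMS arm at three months, when rTMS and sham do not differ at that time. A second, smaller risk is that the within-arm tests are counted in the Bonferroni family and take power from the between-arm contrasts that answer the question.

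**Working it through.** **1. The plan's own figure.** Section 2.10 gives a difference of 1.3, SD 2.9, alpha 0.05 and power 0.80. Taking alpha as two-sided: n = 2 × (1.960 + 0.842)² × 2.9² / 1.3² = 78.1, so 79 per group (80 with the t distribution). The stated 78 is reproduced within rounding. Evaluable patients: 126 × 0.9 = 113 per arm.

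**2. Size of the artefact.** Let the unselected T0 score have mean μ, SD σ and retest correlation ρ. The protocol gives none of these, so all are assumed. With a cutoff of 8 on integer scores:

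- a = (7.5 − μ)/σ and λ = φ(a)/(1 − Φ(a))
- expected fall = (1 − ρ) σ λ
- variance of change = (1 − ρ)² σ² (1 + aλ − λ²) + (1 − ρ²) σ²
- chance of a significant fall in one arm ≈ Φ(fall/SE − z), where SE = SD of change/√113

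Example with μ = 8, σ = 2.9, ρ = 0.7: a = −0.172 and λ = 0.691. The fall is 0.3 × 2.9 × 0.691 = 0.60. The SD of change is 2.14, so SE = 0.202 and fall/SE = 2.98. The chance is Φ(2.98 − 1.96) = 85% at 0.05 and Φ(2.98 − 2.73) = 60% at 0.05/8.

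Over μ 5–12, σ 2.9–4.0 and ρ 0.5–0.9, the expected fall runs from about 0.04 to 2.5 points, and the chance of significance at 0.05 from about 5% to about 100%. It is small when the unselected mean is well above 8 or scores are highly repeatable. These rates ignore the interaction gate and any natural decline.

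**3. With the gate, no rTMS effect at any time.** Simulation with integer scores 0–21, four post-operative times and no time trend: the interaction is significant in about 5% of trials, so a gated within-arm fall is rare (about 1–7% of trials). The between-arm test of change at T3 stays near 5%.

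**4. With the gate, an effect that fades.** Same set-up, with an assumed effect of 1.3 at T1–T3 and zero at T4. The interaction was tested on the three contrasts among T1–T4, as a stand-in for the mixed-model test. The within-arm threshold was 0.05/12. Ranges are over repeated simulations.

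| μ, σ, ρ | Gate opens | Significant T4 fall in rTMS arm, given open gate |
|---|---|---|
| 6, 4.0, 0.7 | 90% | 94–95% |
| 8, 3.5, 0.7 | 97% | 56% |
| 8, 2.9, 0.7 | 99% | 55% |
| 8, 4.0, 0.8 | 98% | 33–35% |
| 10, 2.9, 0.8 | 100% | 4–6% |

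The true T4 effect is zero in every row, and in most of the trials with such a fall the between-arm T4 test was not significant.

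**5. Bonferroni family.** For a 1.3-point between-arm contrast, 1.3 / (2.9 × √(2/113)) = 3.37. With 4 contrasts (0.05/4), power is 80–81%. If 8 within-arm tests (4 times × 2 arms) join the family (0.05/12), it is 68–69%. The lower figures use the t distribution, the upper the normal.

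**The case against.** The strongest reply is that the within-arm tests are gated, secondary and reported beside the group differences, so a reader always has the valid contrast at hand. Much of this stands.

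- A reader might infer that the trial will show significant improvement in either arm by regression to the mean alone. The protocol does not support that. With no effect the tests are reached in only about 5% of trials, and the size of the fall depends on inputs the protocol does not give. A baseline near the peak may even mean an unselected mean well above 8, where regression to the mean is small.
- A reader might infer that the primary result is compromised. It is not: it compares randomised arms and adjusts for baseline HADS-A.
- A reader might infer that the investigators intend to treat a within-arm fall as evidence of efficacy. The protocol nowhere says so; it says only that such changes will be assessed.
- The 12-test family is one reading of an undefined family, and the power loss holds only on that reading. It concerns the contrasts after the interaction test, not the design calculation in section 2.10.
- Selection is on HADS-A alone, so the regression argument does not extend to pain, FRAIL or PSQI.

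The gate and the correction still do not cure the problem. The gate protects when rTMS never works, but an effect that varies over time is what opens it. Bonferroni limits chance error and leaves a systematic fall in place.

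**Conclusion.** The point holds as a minor one. The protocol commits to gated within-arm tests in patients selected on what appears to be their own baseline score. For HADS-A, a significant result from such a test is no evidence of an rTMS effect.

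Under a complete null the problem is rare. Under an assumed effect that has gone by three months, a spurious three-month fall in the rTMS arm follows an open gate in about 4% to 94% of trials. That range rests on an assumed unselected mean of 6–10, SD of 2.9–4 and retest correlation of 0.7–0.8, 113 evaluable per arm and no natural decline. A decline after the peak would add to the fall. The conditional power cost is about 12 percentage points. No between-arm conclusion is biased.

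**What to change.** In section 2.11, state that within-arm HADS-A changes at each time point are reported descriptively, as means with confidence intervals and without tests. Base inference at each time point on baseline-adjusted between-arm differences, and apply Bonferroni only to those contrasts, with their number stated.

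The cost is a change of wording. No data, visits or patients are added, and there are fewer tests to run.
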